## Abstract

**Background:**

Overweight and obesity have a dramatic negative impact on children's health not only during the childhood but also throughout the adult life. Preventing the development of obesity in children is therefore a world-wide health priority. There is an obvious urge for sustainable and evidenced-based interventions that are suitable for families with young children, especially for families with overweight or obese parents. We have developed a prevention program, Early STOPP, combating multiple obesity-promoting behaviors such unbalanced diet, physical inactivity and disturbed sleeping patterns. We also aim to evaluate the effectiveness of the early childhood obesity prevention in a well-characterized population of overweight or obese parents. This protocol outlines methods for the recruitment phase of the study.

**Design and methods:**

This randomized controlled trial (RCT) targets overweight and/or obese parents with infants, recruited from the Child Health Care Centers (CHCC) within the Stockholm area. The intervention starts when infants are one year of age and continues until they are six and is regularly delivered by a trained coach (dietitian, physiotherapist or a nurse). The key aspects of Early STOPP family intervention are based on Swedish recommendations for CHCC, which include advices on healthy food choices and eating patterns, increasing physical activity/reducing sedentary behavior and regulating sleeping patterns.

**Discussion:**

The Early STOPP trial design addresses weaknesses of previous research by recruiting from a well-characterized population, defining a feasible, theory-based intervention and assessing multiple measurements to validate and interpret the program effectiveness. The early years hold promise as a time in which obesity prevention may be most effective. To our knowledge, this longitudinal RCT is the first attempt to demonstrate whether an early, long-term, targeted health promotion program focusing on healthy eating, physical activity/reduced sedentary behaviors and normalizing sleeping patterns could be effective. If proven so, Early STOPP may protect children from the development of overweight and obesity.

**Trial registration:**

The protocol for this study is registered with the clinical trials registry clinicaltrials.gov, ID: ES-2010)

## Background

Overweight is considered to be a global epidemic and the marked increase in childhood obesity is alarming. Preventing the development of obesity in children is therefore a world-wide health priority [1]. Childhood obesity is multi-factorial and has been recognized as heritable [2]. The odds for a child to become obese as an adult increase about threefold if one of the parents is obese and rise tenfold with two obese parents [3]. To which extent this hereditariness is socio-cultural, genetic or epigenetic is unclear [4].

Gain in body weight and fat mass is a consequence of a positive energy balance over time. Thus, it has been suggested that the rise in the obesity prevalence, even in children, is most likely due to the environmental changes, such as easy access to large portions of energy-dense foods or reduced levels of physical activity (PA), particularly in home environment, or a combination of both [5]. Recent research has demonstrated that additional factors, such as sleep patterns, may also play a role in this negative trend in children [6-8]. In spite of the growing evidence for a relationship between sleep duration and weight gain during infancy [7-10] most family-based interventions for pediatric obesity still focus on eating and PA [11], which calls for multifaceted intervention studies including sleep, especially for very young children.

Although, school-based obesity prevention might be successful [12], the overall effectiveness of intervention programs on obesity prevention has been disappointing, especially when it comes to infants and those in the risk groups to develop obesity. Dietary habits in children [13] are also evident in infants [14], proving that obesity-promoting behaviours learned and supported during the early years may lead to lifestyle behaviours that will track throughout the lifespan. We therefore posit that early childhood provides a unique opportunity to establish lifestyle habits that will promote health and minimize the risk of the development of obesity.

Parental involvement is logically important in weight management in overweight children, yet not much is known about the parental role in preventing childhood overweight in the early life years [15]. Parenting skills are the foundation for successful intervention, since they shape the infant's eating, sleep and PA behaviour. Health promoting information and advices are useless unless the parents cooperate; for example, parents, via their dietary knowledge, parenting style and food environment influence children's emerging food choices [16]. Malfunctioning families may benefit less from the intervention programs if the parenting and family function is not taken into account while designing these programs [11]. This introduces the need for both structured and individually targeted interventions in concordance with the individual parent's learning needs (i.e. knowledge deficits, skills, training needs) [11]. The intervention designed here has therefore taken into consideration that (a) obesity promoting behaviours are established early in life, (b) parents play a crucial role in shaping these behaviours, (c) intervening before these behaviours are established is likely to be effective, and (d) that the individually adjusted coaching is likely to facilitate the uptake of consolidation of health promotion messages.

The aim of this paper is to describe and explain the design and evaluation of the Early STOPP intervention, targeting families where one parent is obese or both parents are overweight. The description of the study protocol follows the checklist of the CONSORT statement for cluster randomized trials [17]

## Design and methods

### Study objectives

The objectives of the Early STOPP randomised controlled trial (RCT) is to study whether a targeted intervention can prevent the development of overweight and obesity among pre-school children in families with either one obese or two overweight parents.

Specifically, this RCT aims

• To compare BMI-sds changes from 1 to 6 years of age in intervention and control families

• To identify modifiable habits that promote wellbeing or contribute to reduced obesity development

• To study whether it is possible to introduce and maintain healthy routines concerning PA, sleep and eating habits in children 1-6 years of age.

• To study the interaction between factors of potential importance for weight increase in this age group such as genetics, sleeping patterns, PA, eating patterns, intestinal bacteria and social family factors as well as how they affect a successful obesity prevention in children during the first 6 years of life.

• To identify and analyse barriers in the implementation of the intervention

### Hypothesis

In comparison to the control group, during the course of intervention, children in the intervention group families are expected: to have reduced BMI gain, to consume more fruits and vegetables and less unhealthy foods such as soft-drinks and energy-dense snack foods, to spent more time being physically active and less time sedentary, specifically TV viewing and computer games, to sleep independently and have healthy sleep habits.

### Overall trial design

The Early STOPP study is a RCT with a longitudinal design targeting overweight and/or obese parents visiting Child Health Care Centres (CHCC) within the Stockholm area, as the units of cluster randomization. The intervention will run from 1 year of age to the 6 year of age (school start). The overall study design is summarized in Figure 1.

**Figure 1 F1:**
[figure not shown]
**Diagram of study design and participant flow through the Early STOPP trial**.

### Participants, recruitment and randomization

In total 200 families of different ethnic, socioeconomic and educational background with a child aged 12 month are being recruited at the moment. The included families consist of at least one obese (BMI ≥ 30) or two overweight (BMI ≥ 25) parents. In order to ensure baseline equivalence and minimize selection bias, the overweight and/or obese parents are randomized after recruitment using a computer generated random number schedule developed by a blinded statistician to the Highly Intensive Intervention (HII) and Low Intensive Intervention (LII) groups. The families are informed at baseline on the outcome of randomization prior to the first intervention session. To improve the validity of the measurements of healthy and unhealthy behaviours a Reference group of children (n = 50) with lean parents are being recruited. Representativeness of the trial cohort will continue to be monitored throughout data collection. Health professionals working within the local CHCC are informed about the study through telephone calls, flyers, e-mail bulletins and personal presentations. The parents visiting local CHCC during the routine check up at the age of 8 month are initially approached by the CHCC nurse who gives first brief information about the Early STOPP study and asks if a member of the Early STOPP research team can call and explain more about the study. If so, during the following four months, the Early STOPP team member also answers the questions and if agreed, sends a research information package. The package contains general study information and consent forms.

### Inclusion and exclusion criteria

Parents, at least one obese or two overweight, are eligible to participate if they are able to communicate in Swedish, can freely give informed consent and have a child of one year of age. Infants with chronic health problems that are likely to influence height, weight, levels of PA or eating habits are excluded from this study but are welcome to receive the health promoting information.

### Sample size

The intervention is planned to include 200 families, 100 in each group, providing 80% power at the 5% significance level (double-sided test), considering a 15-20% dropout rate (based on the previous STOPP study). The power calculation is based on detecting a 50% lower prevalence of child overweight and obesity in the intervention group; 20% in the intervention group compared to 40% in the control group.

### Intervention group

The intervention consists of two components, one educational and one individually targeted coaching. The underlying theoretical framework for the intervention is on adult learning theories, academic detailing and coaching [18]. The education and coaching are aimed at raising awareness, increasing parents' knowledge, increasing their self-efficacy to promote parenting behaviour regarding eating, PA and sleep. The multi-disciplinary approach integrates knowledge and methods from medicine, nursing, physiotherapy, dietary or behaviour science. The Early STOPP trial differs from other known prevention programs in the following: a) it starts as early as one year of age, b) aims to effect children's eating, PA and sleep, and c) takes into consideration both parenting skills and parenting style (attitudes that create a certain emotional climate towards eating habits, PA and sleep). The individually adjusted coaching is likely to facilitate the uptake of consolidation of health promotion messages. The key aspects of the Early STOPP program are based on Swedish recommendations for Health Care Centres and include advices on healthy food choices and eating patterns, increasing PA/reducing sedentary behaviour and regulating sleeping patterns.

### Educational component

The educational material (booklets) is developed for correspondent age (1, 2, 3, 4, 5 and 6 years) and is given to the parents/carers to take home during baseline measurements and then during the yearly check up. Advices are based on the latest literature on the subjects of diet, PA and sleeping habits. For example, the sleep part of the intervention methods such as extinction and settled bedtime routines have been tested in treatment of insomnia in childhood, BIC [19,20], as well as sleep and settling behaviors information to parents in the post-natal period has successfully been tested on infants sleep [21].

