### Primary and secondary outcomes

Primary outcome is BMI sds-score and the secondary outcomes are PA, sedentary behaviour, motor function/development, sleeping habits, food intake, eating patterns and quality of life. These outcomes require repeated collection due to the rapid changes in height, weight, eating, motor development and PA behaviours in infants. They will therefore be measured at baseline (1 year of age) and yearly thereafter. For children in the intervention group, height, weight and waist circumference are measured every 6 month. Metabolic profile indicators, secondary outcomes, as reflected in biomarkers will be collected at the age of 1, 3 and 6.

Data on demography and socio-economic status is collected by self-report. Parent and infant data is collected by parental/carer self-completed questionnaires and objective measures (Table 1). The questionnaires include already existing validated questionnaires as well as additional questions developed by the Early STOPP project team for topics not reflected in the existing questionnaires. The questionnaires are completed by each parent separately at home before the annual visit. Together these questionnaires take between 30-45 minutes to complete.

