### Dietary intake and eating behaviour

A four-day estimated food diary, covering two weekdays and two weekend days, will assess the children's dietary intake. This diet assessment method is chosen since both qualitative and quantitative aspects of the children's diet intake will be evaluated [28]. The parents' diet quality will be assessed using a semi-quantitative food frequency questionnaire (FFQ) developed and validated by the Swedish National Food Administration. To measure children's eating habits; the Children's Eating Behaviour Questionnaire (CEBQ) will be used [29]. The CEBQ is a multi-dimensional, parent-report questionnaire aims to provide a useful measure of eating styles to study the early precursors of obesity and eating disorders. The CEBQ consists of 35 statements originally derived from interviews with parents about their children's eating behaviour and the literature on the subject. Originally the items covered eight dimensions (factors) of eating style: Food Responsiveness (FR), Emotional Over-Eating (EOE), Enjoyment of Food (EF), Desire to Drink (DD), Satiety Responsiveness (SR), Slowness in Eating (SE), Emotional Under-Eating (EUE) and Food Fussiness (FF).

Outcome measures from the food diary, FFQ and CEBQ will be energy and nutrient intake, meal patterns, times and quantity of vegetable and fruit intake as well snacking patterns.

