### Physical Activity, sedentary behaviour and motor function

Parents will report the frequency and duration in health related PA and sedentary behaviour during the previous week using the International Physical Activity Questionnaire (IPAQ), long version [30] at baseline. This is done to be able to compare with national PA data. When the children are 2, 3, 4, 5 and 6 years of age the parents will answer a question about their leisure time PA in the past 12 months [31]. This is done to get a crude measure of the parent's PA levels over a year. Further, the parents will also report the number of hours their child typically spends playing outdoors on weekdays and weekend days. In addition, every year, parents and the child's PA and sedentary behaviour will be assessed objectively using the ActiGraph GT3X+ accelerometer (ActiGraph, LLC, Fort Walton Beach, FL). The ActiGraph has shown high agreement with energy expenditure and measures of time spent in different intensities for adults as well as for children 3 year and up [32-34]. A calibration study on children 2 years of age will be performed within the Early STOPP project. Outcome measures from the accelerometer will be total PA expressed as counts per minute, time spent in different intensities of PA as well as sedentary time. The families will get verbal and easy to read instructions from the research staff on how to wear the accelerometer (around the non-dominant wrist using an elasticated belt). The participants are asked to wear the accelerometer for seven consecutive days, but for the analysis we will include participants that have at least four days of measurements [35].

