## Planned data analysis

To achieve a normal distribution the variables will be transformed if needed or non-parametric statistics will be used. Analysis of covariance will be used to test for differences in baseline characteristics between the study arm and adjustment will be made to analyses as required. An estimation of intervention effect on outcome measures will assessed at each follow-up observation (every year post-baseline) on an intention to treat basis. A mixed model will be used to test the average effect of the intervention after taking account of baseline covariates.

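### The age-1 food diary and accelerometry may be recorded after families know their arm and hold the intervention booklet

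*Protocol article*

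**What the plan says.** The Intervention group section of the protocol article names two components, education and coaching. Under Educational component, the booklet that carries the education "is given to the parents/carers to take home during baseline measurements and then during the yearly check up". Its content overlaps with the secondary outcomes: "Advices are based on the latest literature on the subjects of diet, PA and sleeping habits".

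Under Participants, recruitment and randomization, "The families are informed at baseline on the outcome of randomization prior to the first intervention session". The limit set there is the start of the sessions, not the completion of baseline data.

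On the outcomes, Primary and secondary outcomes says: "They will therefore be measured at baseline (1 year of age) and yearly thereafter". Table 1 marks the diet diary and the physical-activity accelerometer at age 1. Both run over several days. The diary is described as "A four-day estimated food diary, covering two weekdays and two weekend days". For accelerometry, "The participants are asked to wear the accelerometer for seven consecutive days", and "The families will get verbal and easy to read instructions from the research staff on how to wear the accelerometer". Neither section places these days before or after the baseline visit, disclosure or handover.

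Planned data analysis provides for a test of baseline differences between arms, with adjustment where required. It then provides for a mixed model of the intervention effect "after taking account of baseline covariates".

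**The concern.** A baseline value is safe to test or adjust for because treatment cannot have changed it. That protection is lost once a family knows its arm, and more so once an intervention family has taken home advice on diet and activity. The sequence as written allows both to happen before a four-day or seven-day record is complete.

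Two consequences would follow for diet, physical activity and sedentary time. First, the baseline comparison could flag an imbalance that the trial itself produced. Second, adjusting for the shifted value would remove part of the real effect. These are named secondary outcomes and part of the stated hypothesis. An analysis plan cannot fully repair the problem, because it arises when the data are collected.

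**Working it through.** **The plan's own figure.** The article gives no number on this point. Its sample size does not depend on it, and it reproduces: 40% against 20%, two-sided 5%, 80% power and pooled variance need 82 per arm. Then 82/0.85 gives 97 and 82/0.80 gives 103, against the stated 100.

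**Step 1: order of events.**
- Disclosure: at baseline, with the first intervention session as the only deadline.
- Booklet: during baseline measurements.
- Diary: four days. Accelerometer: seven days. Both are due at age 1, and neither can be completed within a single visit.
- Position of those days relative to the visit: not stated. That staff give the wearing instructions suggests wear after contact with staff, but does not establish it.

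The text therefore allows the records to fall before, across or after disclosure and handover. Only the first order is safe, and nothing requires it.

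**Step 2: which baselines are exposed.**
- Food diary and accelerometry: exposed.
- Questionnaires: completed at home before the annual visit (Primary and secondary outcomes), so ahead of a booklet handed over at that visit.
- Sleep: no age-1 measurement in Table 1; first measured at age 2.
- BMI-sds: from height and weight taken by trained staff, which a booklet given at the same visit cannot alter.

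**Step 3: size of the bias.** Work in SD units, with higher values better. Let T be the true effect, b the slope of follow-up on baseline, and d the early shift in the intervention arm minus that in the control arm. The baseline-adjusted estimate is

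(difference in follow-up means) − b × (difference in baseline means).

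Randomization makes the expected baseline difference zero. An early shift makes it d. The expected estimate is then T − b × d, so the bias is −b × d.

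The article gives neither b nor d. On assumed ranges, b × d in SD is:

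| b | d = 0.05 | d = 0.1 | d = 0.2 |
|---|---|---|---|
| 0.2 | 0.01 | 0.02 | 0.04 |
| 0.5 | 0.025 | 0.05 | 0.10 |
| 0.7 | 0.035 | 0.07 | 0.14 |

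**Step 4: the same as a share of the effect.** If a fraction f of the later effect is already present at baseline, then d = f × T and the adjusted model keeps 1 − b × f. With equal SDs at both times, b is the correlation. For assumed b of 0.3 to 0.7 and f of 0.10 to 0.50, the share kept runs from 1 − 0.7 × 0.50 = 65% to 1 − 0.3 × 0.10 = 97%.

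**The case against.** **The order is only unstated, and an article may leave it to procedures.** Data handling refers to standard operating procedures that are not shown, and they may already put the records first. This stands in part: nobody can say from the article that any record was taken late. But the article is not merely silent. It places delivery of an active component inside the baseline measurements and ties disclosure to the first session rather than to complete data. If the procedures are stricter, the text should say so.

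**Controls receive something too.** Under Control group, they get a general health newsletter at baseline. This stands. The bias depends on the difference in shift between the arms, so any control response in the same direction reduces d.

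**The analysis may not use these values.** Planned data analysis speaks of baseline covariates without naming diary or accelerometer values. This also stands, so the bias arises only where they are tested or adjusted for.

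**The slope may be small.** The article reports accelerometer agreement for children from 3 years and plans a calibration study at 2, so a strong slope from age 1 cannot be presumed. The assumed range therefore starts at 0.2.

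**The direction is conservative.** For genuine early change, the bias is towards no effect and does not create a false positive. This limits the weight of the point but does not remove it.

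**Conclusion.** The point holds for two measures, the age-1 food diary and accelerometry. As written, they may be recorded after allocation is known and the booklet is in the home. Where they are tested or adjusted for, genuine early behaviour change would bias the diet, physical-activity and sedentary effects towards zero by about b × d. The size is unknown: about 0.01 to 0.14 SD on the assumed ranges, none of which comes from the article.

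A reader might infer more, but the article does not support it:
- *That these baselines are in fact collected in the days after disclosure.* No section says so.
- *That all behavioural baselines, or the primary outcome, are compromised.* The questionnaires precede the visit, sleep has no age-1 value, and BMI-sds is not affected.
- *That a quarter to a half of the detectable effect is lost.* That takes the single assumed pair b = 0.5 and d = 0.2 SD and compares 0.10 SD (adjusted) and 0.20 SD (change score) with about 0.45 SD for 80 per arm. This benchmark is not in the protocol, which is powered on prevalence. A change analysis is stated for BMI-sds but not for activity or diet.

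**What to change.** **Families still to be enrolled.** Amend Participants, recruitment and randomization and Educational component so that the baseline diary and accelerometer week are completed and returned before allocation is disclosed and the booklet is given, for example at the first coaching session. State the same order where the diary and accelerometer are described.

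**Families already handled otherwise.** Where disclosure dates are available, run a sensitivity analysis that omits diary and accelerometer baselines recorded after disclosure as covariates. The article does not say that these dates are recorded, so this should be checked first.

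**Cost.** Allocation news and the booklet come a week or two later. Coaching is a separate appointment, at home or on request at the clinic, so handover there adds no visit. Recruitment is under way, with baseline measurements expected to finish by Autumn 2011, so the reordering protects only later families.
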